## Abstract

**Background:**

Alzheimer’s disease (AD) is a major public health issue. Cognitive interventions such as computerized cognitive trainings (CCT) are effective in attenuating cognitive decline in AD. However, in those at risk of dementia related to AD, results are heterogeneous. Efficacy and feasibility of CCT needs to be explored in depth. Moreover, underlying mechanisms of CCT effects on the three cognitive domains typically affected by AD (episodic memory, semantic memory and spatial abilities) remain poorly understood.

**Methods:**

In this bi-centric, randomized controlled trial (RCT) with parallel groups, participants (planned *N* = 162, aged 60–85 years) at risk for AD and with at least subjective cognitive decline will be randomized to one of three groups. We will compare serious game-based CCT against a passive wait list control condition and an active control condition (watching documentaries). Training will consist of daily at-home sessions for 10 weeks (50 sessions) and weekly on-site group meetings. Subsequently, the CCT group will continue at-home training for an additional twenty-weeks including monthly on-site booster sessions. Investigators conducting the cognitive assessments will be blinded. Group leaders will be aware of participants’ group allocations. Primarily, we will evaluate change using a compound value derived from the comprehensive cognitive assessment for each of three cognitive domains. Secondary, longitudinal functional and structural magnetic resonance imaging (MRI) and evaluation of blood-based biomarkers will serve to investigate neuronal underpinnings of expected training benefits.

**Discussion:**

The present study will address several shortcomings of previous CCT studies. This entails a comparison of serious game-based CCT with both a passive and an active control condition while including social elements crucial for training success and adherence, the combination of at-home and on-site training, inclusion of booster sessions and assessment of physiological markers. Study outcomes will provide information on feasibility and efficacy of serious game-based CCT in older adults at risk for AD and will potentially generalize to treatment guidelines. Moreover, we set out to investigate physiological underpinnings of CCT induced neuronal changes to form the grounds for future individually tailored interventions and neuro-biologically informed trainings.

**Trial registration:**

This RCT was registered 1st of July 2020 at clinicaltrials.gov (Identifier NCT04452864).

**Supplementary Information:**

The online version contains supplementary material available at 10.1186/s12888-022-04131-7.

## Introduction

### Background

Alzheimer’s disease (AD) is a leading cause of disability and a major health- and societal issue. Although the clinical presentation at mild or early stages may vary [1], AD typically affects three cognitive domains: episodic memory (EM), semantic memory (SM), and visuospatial abilities (SA [2];). The pathophysiological chain of events in neurodegenerative dementias commences decades before the onset of clinically relevant symptoms [3]. Of note is that subjective cognitive decline (SCD), defined as self-perceived decrease in cognitive performance, is considered an early at-risk state for progression to AD especially when the perceived decline is worrisome [4]. Here, despite scoring within normal range in neuropsychological test, people with SCD have a somewhat altered cognitive performance profile with lower results in EM tasks compared to healthy controls [5, 6].

The long phase before onset opens the possibility to alter the disease course and to postpone symptom manifestation. To date, pharmacological agents to counteract early cognitive dysfunction in the elderly are limited [7, 8], which gave rise to the development of cognitive interventions. As one sub-category of cognitive interventions, cognitive stimulation is defined by the activation of broad memory patterns and is well established in clinical settings and part of many interventional guidelines for the treatment of manifest dementia. However, cognitive training (CT) on the other hand is far more domain specific and focuses on guided practice on a set of tasks that reflect particular cognitive functions. CT is thought to attenuate cognitive decline related to aging as well as disease-related decline [9, 10]. Further, limited evidence indicates that those beneficial effects remain observable even several years after intervention [11]. Positive effects were reported in multiple cognitive domains, including memory, reasoning, and speed of processing [11–13].

Crucially, as AD typically impacts episodic memory, semantic memory and visuospatial abilities [14–16], any CT against symptoms of AD should thus focus on these three domains and may also include training of working memory (WM). Adding a WM component to the training provides the possibility of far transfer benefits to other cognitive domains and utlimately to every-day life functioning [17].

#### Rationale of computerized cognitive training

Computerized cognitive training (CCT) has benefits over other types of CT as it readily lends itself to home-based use and individualized training protocols. For example, a study including 42 patients with amnestic mild cognitive impairment (MCI) found training using a tablet computer to robustly improve episodic memory function, while additionally enhancing visuospatial abilities [8]. Although direct comparisons are difficult, a current meta-analysis indicates that computer-based interventions outperforms therapist-led trainings in MCI [18]. Comparing CCT by content, training of multiple-domains outperformed single domain trainings [19]. Multi-component CCT has beneficial effects on a number of cognitive aspects such as global cognition, attention, working memory [11] as well as processing speed [12] and delayed recall [13].

The ultimate goal of CT, transferring its effects to activities of daily life or cognitive tasks regarding different cognitive domains (far transfer), is particularly difficult to achieve when the trained task is too narrowly designed. Theoretical frameworks for the investigation of transfer effects have been established [20]. Interestingly, when examining predictors of transfer from WM training, lower baseline performance predicted higher gains [21]. That same study indicated that old age was associated with lower gains on visuospatial WM tasks.

Discordant conclusions concerning optimal training protocols also affect CCT interventions [22]. Existing studies indicate that CCT for elderly individuals is best done in groups at an institution setting rather than at home to ensure good adherence i.a. due to social affiliation. A meta-analysis focusing on intervention characteristics, showed that CCT yields greater effect sizes when trained more than 3 times per week (*p* = 0.042), more than 8 total training weeks (*p* = 0.003) and more than 24 training sessions (*p* = 0.040) [19, 23]. However, reviews on the current state of research highlight the inconclusiveness on the best training protocols and the necessity of comprehensive and longitudinal assessments of a broad range of cognitive functions, including generalization of benefits from trained tasks to other cognitive activities (far transfer) [6].

Concluding from previous findings, we aim at specifically training episodic memory, semantic and spatial abilities and working memory while complying to recommendations for effective training protocols.

#### Neuroimaging

One crucial part to in-depth understanding of CCT effects and mechanisms is situated in its’ physiological and more specifically neuronal correlates. Several studies have combined cognitive training with magnetic resonance imaging (MRI) to investigate neuronal changes resulting from cognitive training [24, 25]. Imaging can be employed to demonstrate target engagement and underlying mechanisms by measuring brain changes over the intervention period [26]. Here, functional MRI (fMRI) can help to distinguish changes in the network underlying the task specifically trained (e.g., hippocampus in an episodic memory task) from changes in neuronal processing observable outside the task-specific network where they may play a compensatory role. Data on functional brain changes due to CT showed increased as well as decreased activity after the CT [27]. However, these differing findings are probably caused by the complex relationship between task performance and changes in brain activity. If increased brain activity after CT is associated with increased task performance, this might indicate successful compensatory brain activity [28]. Stable performance in combination with decreased brain activity after CT on the other hand might indicate more efficient task processing as a consequence of the CT.

In summary, possible task fMRI results indicating beneficial CT in older adults at risk of AD are:I.Decrease in task-related brain network activity after CT and constant task performance as a consequence of more efficient task processingII.Decreased activity in brain regions outside the task-related network because brain regions within the task-related network are more active againIII.Increased activity in previously hypoactive task-related brain network and increased task performance through CT (restoration)IV.New activity in brain areas not active before CT (new compensatory activity) and increased task performance

Apart from task related fMRI, resting state fMRI (rsfMRI) provides valuable information about functional brain connectivity. This technique is often used to investigate structures like the default mode network (DMN), which consists of several brain areas particularly active during rest [29]. Another network often investigated in association with dementia is the central executive network (CEN) which is active during demanding tasks like working memory. Alterations within the DMN and CEN network have frequently been associated with dementia. In the context of AD for example, a decrease in the DMN connectivity has been reported repeatedly. Multi-domain CCTs were able to increase the connectivity between the hippocampus and frontal as well as the temporal brain areas during rest. Furthermore, connectivity within the DMN and CEN could be increased through a multi-domain cognitive training [10, 30].

Another useful technique to depict cerebral blood flow (CBF) is Arterial spin labelling (ASL), a non-invasive alternative to positron emission tomography. Several studies reported a pattern of hypoperfusion in MCI and dementia due to AD especially in the precuneus and posterior cingulate gyrus [31, 32]. Moreover, reduced blood flow in medial-temporal and parietal brain regions was associated with increased decline of functioning in daily life in healthy older adults or participants with MCI across 3 years [33]. Interestingly, cognitive training was able to increase global CBF in parieto-frontal regions in a sample of healthy older adults. This might indicate a possibility to reverse hypoperfusion, even in normal aging [34].

Apart from effects on functional brain activity, structural brain changes have been reported after CT as well. Nguyen et al. [27], for example, reported that CT may lead to increased grey matter volume or attenuate age related cortical thinning.

#### Blood measures

Blood measures are another way to estimate age or AD related brain changes. The presence of the Met-allele in the brain-derived neurotrophic factor (BDNF) genotype was associated with an decreased hippocampal volume in young adults [35] and an increased rate of cognitive decline in middle aged adults in episodic memory and executive functions across more than 6 years [36]. The apolipoprotein E (ApoE) 4 allele is a risk factor for AD. In the context of CT, it seems that ApoE non-carriers benefit more from a CT than carriers. But data about the moderating effect of ApoE on CT benefits is scarce and more studies are needed [37]. To estimate brain pathologies possibly indicating AD (e.g., amyloid plaques and tau fibrils), new blood plasma based measures of amyloid beta and phosphorylated Tau exists. These measures showed the ability to differentiate between amyloid PET positive and negative participants [38–40].

### Objectives

The main objective of this study is to train cognitive domains typically affected by AD through a serious game-based CCT and to assess the training effect on cognition and neural parameters of older adults in an at-risk or manifested stage of AD relative to an active and a waitlist control group. We set out to combine direct training of episodic memory, semantic, and spatial abilities with working memory training to facilitate transfer to every-day functioning. By combining group- and at-home based training elements, while integrating collaborative social elements both within the app as well as during the group sessions, we expect high adherence. In summary, the purpose of this study is 1) to investigate the effectiveness of our CCT on the three cognitive domains typically affected in AD, 2) investigate transfer effects and 3) to explore the neuronal underpinnings of the CCT.

We hypothesized that participants enrolled in the CCT group will show larger and more durable improvements in cognitive performance after training compared to those in either the active control group or the waitlist control group. We expect changes in functional brain activity to be observed during rest (i.e., increased connectivity in the DMN/CEN and increased CBF). Based on the findings reported in the previous section [10], we also expect increased functional connectivity between the hippocampus and frontal as well as temporal brain areas. In task fMRI, we expect indications for more efficient task-specific networks. When keeping the number of solved trials constant (e.g., in an externally paced task protocol) we expect declining activity due to higher task efficacy in the intervention group. In the self-paced SA task, we expect more solved trials in all participants but less activity increase in task-related networks after training compared to baseline activity. This finding would again reflect more efficient networks [28]. Furthermore, we aim to identify factors that moderate the magnitude of these effects. As shown in our previous cognitive training study [41], participants with less advantageous cognitive profiles at baseline, particularly, may benefit from cognitive interventions. Other factors which might moderate training benefits are blood and genetic markers like ApoE 4 genotypes and plasma amyloid which will also be analyzed during this study.

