### Participant timeline

Participants will receive information that they will undergo a cognitively activating serious game-based computerized training starting either immediately or after a 3 months’ observation period but without knowing the distinction between the CCT and the active control group. Staff conducting the cognitive testing will be blinded to the study arm. The training will be conducted in small groups of 3–6 participants. The training group immediately starts with the CCT for 10 weeks, including weekly group sessions and will subsequently perform the training for twenty more weeks with monthly booster sessions. The waitlist control group will start the CCT with a delay of 10 weeks. The active control group will perform 10 weeks of unspecific cognitive activation (watching documentaries) before subsequently starting the CCT for 10 weeks. Ten weeks after the fourth assessment (i.e. after 3 × 10 weeks), all participants will be followed-up with a parallel version of the COGTEL.

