### Intervention description

Based on literature and standardized cogntive tests, we designed four tablet-based training games for each of the three key cognitive domains specifically affected by AD (episodic memory, semantic memory and spatial abilites) in addition to WM-based training. All games are fully developed in-house, programmed in unity (http://unity3d. com/) and provided on 10.2 in. iPads. Individual games are connected by an overarching story-line (a sailboat traveling from one island to the next where each island represents a game) and are performed repeatedly within sessions. A detailed description of each game can be found in the supplementary material (see Additional file 1).

During most on-site group sessions (week 1–4, 6, and 8), two new training games are introduced and practiced with the support of the investigators. The games are distributed in an accumulative pseudo-randomized order to balance between memory components. Each game consists of different levels of difficulty and adapts automatically to the abilities of the participants. Furthermore, cooperative elements like a puzzle which can be solved as a group provides a social experience. According to recommendations of a recent meta-analysis, participants play the games daily for 24 minutes, i.e., three games for 8 minutes each [23]. The study design thus required between 50 and 150 days with training sessions depending on the study arm, resulting in each game being played at least 12 times. Before every at home training session participants will be asked to rate their motivation for the session and how they feel at the moment. After each session, they subjectively will rate their performance.

After 1 week of playing each game, we will assess game perception using the game perception questionnaire [45, 46]. General gaming experience is assessed with the core elements of gaming experience questionnaire (CEGEQ) [47].

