### Explanation for the choice of comparators: active control group and waitlist control group

To test whether potential improvements in the intervention group result specifically from the training and not just from e.g. meeting as a group or performing an activating task, we use an active control group. To match the at-home element of the intervention group participants in the active control group will be asked to watch documentaries on the tablet computer matched for time and frequency of the CCT. To ensure that the participants are attentively watching the videos, pop-up windows with easy to solve multiple choice questions (e.g. “What is 2+3?”) randomly appear during the documentaries sessions. This active control condition aims to include the same level of social interaction in a group setting again matched for duration and frequency but without explicit cognitive training. To this end, participants are asked to discuss the documentaries with the other group members. Additionally, participants will play group games that are not cognitively demanding and where success is based on chance rather than skill (e.g., Bingo in slow speed). The active control intervention lasts 10 weeks. Afterwards, participants perform the same CCT as the intervention group.

Before staring the CCT, the wait-list control group will have a 10-week passive waiting period after the first cognitive assessment and MRI scan. The waitlist control group will allow us to quantify test-retest effects as well as habituation to the MRI scanner setting as in previous work by others [48].

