### Strategies to improve adherence to the intervention and to promote participant retention

As previous CCT studies often faced mal-adherence, we included weekly groups sessions to not solely have a training purpose but to also encourage social interaction among participants. Additionally, based on research on the most useful intervention protocols, we encouraged daily training and followed up with booster sessions over 6 months for long-term benefits in the intervention group. Game characteristics favorable for training success such as a challenging but playful design were implemented based on previous research findings [49, 50]. To promote motivation and to provide direct assistance, participants are called after their first at-home training and a help button within the app triggers an automated e-mail to the investigator. Response data is transmitted to the investigator to track compliance to the training protocol and to provide low-threshold support in case of difficulties or potential non-adherence.

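### Both control groups start the same CCT after the second assessment, so the hypothesis of more durable improvement than control cannot be tested as worded

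*Protocol article*

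**What the plan says.** A1 to A4 denote the four cognitive assessments. All places are in the Protocol article.

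- **Objectives.** The CCT group is expected to show "larger and more durable improvements in cognitive performance after training compared to those in either the active control group or the waitlist control group".
- **Participant timeline.** The CCT arm trains for 10 weeks and "will subsequently perform the training for twenty more weeks with monthly booster sessions". The active control watches documentaries for 10 weeks and then has 10 weeks of CCT. For the third arm, "The waitlist control group will start the CCT with a delay of 10 weeks"; the text does not say how long its CCT lasts. Ten weeks after A4, "all participants will be followed-up with a parallel version of the COGTEL".
- **Choice of comparators.** On the active control: "Afterwards, participants perform the same CCT as the intervention group".
- **Training load.** Abstract, Methods: "Training will consist of daily at-home sessions for 10 weeks (50 sessions) and weekly on-site group meetings". Intervention description: "The study design thus required between 50 and 150 days with training sessions depending on the study arm".
- **Assessment times.** Outcomes gives intervals of about 10 weeks; the Fig. 1 caption gives 3 months.
- **Analysis.** Sample size sets the primary test as a repeated-measures ANOVA with three groups and two time points, and also powers a group by four-time-point interaction. Statistical methods plans linear mixed models over all time points.
- **Purpose of the later phase.** The adherence section says the design "followed up with booster sessions over 6 months for long-term benefits in the intervention group". The Discussion names both dose-response and the duration of CCT effects as things the design can address.

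**The concern.** Durability relative to a control condition needs a comparator that stays under that condition while gains are followed. Here both control conditions end at about A2. A reader who takes the hypothesis at its word will look for the CCT arm to be ahead of the controls at A3 or A4 and will call that durability.

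That reading can point the wrong way. If CCT produces a lasting gain and more training adds nothing, the controls catch up once trained, and the arms do not differ at A4. If the gain disappears when training stops, the CCT arm is ahead at A4 because it has kept training and the active control has not. A lasting gain plus a dose effect also puts the CCT arm ahead. At stake is the trial's longer-term conclusion, not its primary result.

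**Working it through.** **1. The plan's own sample sizes.** Noncentral F for the group by time interaction, with λ = f²(N − 3)(m − 1)ε, df1 = 2(m − 1)ε, df2 = (N − 3)(m − 1)ε, f = 0.25 and α = 5%.
- m = 2, ε = 1, N = 162: λ = 0.0625 × 159 = 9.94; power 0.805.
- m = 4, ε = 0.75, N = 96: λ = 0.0625 × 93 × 2.25 = 13.08; power 0.813.

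Both stated figures reproduce and are not in question.

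**2. Exposure.** 50 sessions in 10 weeks is 5 per week, and 150/5 = 30 weeks = 10 + 20, which is also three 10-week intervals. Cumulative weeks of CCT on the 10-week calendar:

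| Arm | A1 (wk 0) | A2 (wk 10) | A3 (wk 20) | A4 (wk 30) | COGTEL (wk 40) |
|---|---|---|---|---|---|
| CCT | 0 | 10 | 20 | 30 | 30 |
| Active control | 0 | 0 | 10 | 10 | 10 |
| Waitlist, if CCT lasts 10 weeks | 0 | 0 | 10 | 10 | 10 |
| Waitlist, if CCT lasts 20 weeks | 0 | 0 | 10 | 20 | 20 |

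No assessment after A2 has an untrained arm.

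**3. What a CCT versus active control difference at A4 can mean.** Assumptions: 54 per arm; one arm differs from two equal ones, so d = 0.25/(√2/3) = 0.530 SD of change; compound symmetry, so every change score has SD 1. Two-sided t test, df = 106, noncentrality δ√(54/2) for a true difference of δ SD. The retention and dose patterns are illustrative; none comes from the article.

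| Truth | Difference at A4 | Noncentrality | Rejects |
|---|---|---|---|
| Gain lasts, extra training adds nothing | 0 | 0 | 5% |
| Gain present only during training | 0.53 | 2.76 | 78% |
| Gain lasts, 20 more weeks add 0.53 SD | 0.53 | 2.76 | 78% |
| Gain lasts, 20 more weeks add 0.27 SD | 0.27 | 1.38 | 28% |

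The second and third rows agree because the added gain was set equal to the first. They show that opposite truths about retention can give the same contrast. If the correlation instead falls as 0.5 per interval, the last three rows become 54%, 54% and 18%.

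**4. What the design can say about retention.** The active control is off CCT between A3 and A4. So is the waitlist arm if its CCT lasts 10 weeks; the two controls can then be pooled (n = 108).

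| A3-to-A4 change | Formula for noncentrality | Full loss (0.53) | Half loss (0.27) |
|---|---|---|---|
| Active control, within arm | δ√54: 3.90; 1.95 | 97% | 48% |
| Both controls pooled, within arm | δ√108: 5.51; 2.76 | over 99% | 78% |
| Active control relative to CCT arm | δ√(54/2): 2.76; 1.38 | 78% | 28% |
| Both controls relative to CCT arm | δ/√(1/54 + 1/108): 3.18; 1.59 | 89% | 35% |

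For the active control alone, the 95% half-width is 2.006/√54 = 0.27 SD within arm and 1.983 × √(2/54) = 0.38 SD relative to the CCT arm, that is 51% and 72% of the assumed gain. The relative contrast allows for retest effects, but it also moves if the CCT arm keeps improving. With active control alone it rejects 28% of the time under full retention if the CCT arm gains 0.27 SD from A3 to A4.

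**The case against.** The strongest defence is that the hypothesis compares arms as randomised, with schedules openly described, so the later contrast can be read as early/extended against delayed/shorter CCT. The adherence section and the dose-response remark in the Discussion suggest that this contrast is wanted, and it is a valid randomised comparison. The article ties its main hypothesis to the two-time-point ANOVA and names no A3 or A4 between-arm test of durability. All of this stands. It does not rescue the wording, which sets CCT against two control groups whose conditions have ended by A3. No SAP can restore an untrained comparator.

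Three stronger readings are tempting but not supported:

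- **That the four-time-point interaction is the durability test.** The article powers it but never gives it that role.
- **That retention in the CCT arm rests on the COGTEL alone.** This requires A4 to fall at the end of training. The Participant timeline and Outcomes sections favour that, as does the Discussion's 9 months of training if matched to three 3-month intervals. But 30 weeks of training with 3-month spacing (A4 at about week 39) would put A4 about 9 weeks after training stopped. The Discussion also mentions follow-up visits after study completion without saying what they are.
- **That power for half loss is only 48%.** That holds for the active control alone. If the waitlist CCT lasts 10 weeks, pooling gives 78%.

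**Conclusion.** The point holds for the durability half of the hypothesis. Only A1 to A2 compares CCT with no CCT; the primary analysis and the claim of larger improvement over that interval are unaffected. From A3 onwards a between-arm difference reflects the timing and amount of CCT. It cannot separate gains that vanish off training from lasting gains with a dose effect, and a fully lasting gain without a dose effect shows no difference.

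The crossover of both controls rests on the text alone and holds on either assessment calendar and for either waitlist duration. The rejection rates rest on the assumed 0.53 SD gain, 54 per arm, compound symmetry and the illustrative patterns. The design does carry some information on duration, but chiefly within the control arms after they have been trained. The wording should be corrected because it governs what the trial may later claim.

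**What to change.** - Limit claims of superiority over the control conditions to A1 to A2.
- Reword the later part of the hypothesis as immediate/extended versus delayed/shorter CCT at A3 and A4, in line with the dose-response aim.
- State retention after CCT ends as a separate, largely within-arm aim. Assess it in the planned mixed model by the A3-to-A4 change in whichever arms are then off CCT: the active control, plus the waitlist arm if its CCT lasts 10 weeks. Read it together with the same change in the CCT arm, since neither contrast is enough alone.
- State how long the waitlist CCT lasts and when A4 falls relative to the end of training. If A4 falls at the end of the CCT arm's 30 weeks, say that this arm has no off-training domain composite among A1 to A4.

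The cost is text only, with no added visits or participants. The price is a weaker durability claim that is no longer a comparison with an untrained control and has limited power for partial loss.
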